## Abstract

**Background:**

Mild cognitive impairment (MCI) is an intermediate state between normal aging and Alzheimer’s disease, which is the world’s most common form of dementia. It is important to identify early and easily available interventions to delay the progression of MCI to Alzheimer’s disease. Acupuncture has been reported to improve the clinical outcomes of MCI treatment. Acupuncture is a complex intervention, involving both specific and non-specific factors associated with therapeutic benefits. Therefore, we intend to obtain basic data for developing an optimal acupuncture treatment for MCI by comparing the effects of different acupuncture treatment methods on cognitive function in MCI patients.

**Methods:**

This study will be a prospective, outcome-assessor-blinded, parallel-arm, single-center (DongShin University Gwangju Korean Medicine Hospital, Republic of Korea), randomized controlled clinical trial. Thirty-two participants with MCI will be randomized in equal numbers to four groups (basic acupuncture (BA), acupoint specificity (AS), needle duration (ND), or electroacupuncture (EA)) and receive acupuncture treatment once per day, 3 days/week for 8 weeks. The BA and ND groups will receive acupuncture treatment for 30 and 20 min, respectively, at Baihui (GV20), Sishencong (EX-HN1), Fengchi (GB20), and Shenting (GV24). The EA group will receive electroacupuncture treatment at the same acupoints for 30 min. The AS group will receive acupuncture treatment at GV20, EX-HN1, GB20, GV24, and Taixi (KI3) for 30 min. The outcome measured will be scores on the Korean version of the Alzheimer’s Disease Assessment Scale—cognitive subscale, the Korean version of the Montreal Cognitive Assessment, the Center for Epidemiological Studies Depression scale, the Korean Activities of Daily Living scale, the Korean Instrumental Activities of Daily Living scale, and the European Quality of Life Five Dimension Five Level scale. All scores will be recorded before intervention, 8 weeks after the first intervention, and 12 weeks after completing the intervention.

**Discussion:**

Four acupuncture protocols will be assessed and compared as potential MCI treatments. This study is expected to provide data to be used in developing an optimal acupuncture method for MCI treatment.

**Trial registration:**

Clinical Research Information Service, KCT0003430. Registered on 16 January 2019.

http://cris.nih.go.kr).

**Electronic supplementary material:**

The online version of this article (10.1186/s13063-019-3670-3) contains supplementary material, which is available to authorized users.

## Background

Mild cognitive impairment (MCI) is defined as a subjective and objective decline in cognition and function greater than expected for an individual’s age and education level, which neither meets the criteria for diagnosis as dementia nor is severe enough to interfere with activities of daily living (ADL) [1, 2]. MCI represents a significant risk factor for the development of dementia and is the primary target for early detection and management of dementia [3, 4].

Currently, there is no approved pharmacological treatment for MCI [2]. Systematic reviews and meta-analyses evaluating the efficacy of cholinesterase inhibitors (such as donepezil, rivastigmine, and galantamine) for MCI treatment have concluded that there is no convincing evidence that cholinesterase inhibitors have an effect on cognitive test scores or the progression of MCI to Alzheimer’s disease [5, 6]. There is some evidence suggesting that nonpharmacological interventions such as cognitive training [7], physical exercise [8], and acupuncture [9, 10] might be beneficial for patients with MCI. However, there is currently no established treatment method for MCI [4].

Acupuncture is a core component of traditional Chinese medicine; recent systematic reviews of the limited evidence in the literature suggest that acupuncture might improve cognitive function and ADL in patients with cognitive impairment and dementia [11–13]. However, each clinical trial to date has used a different acupuncture treatment method. Apart from needle insertion, factors such as needling sensation, psychological factors, acupoint specificity, acupuncture manipulation, and needle duration also influence the therapeutic effects of acupuncture [14].

Although acupuncture is used for MCI treatment in Korean medicine, no studies have been conducted to develop an optimal acupuncture treatment method for this condition. Therefore, through this proposed randomized controlled trial, we intend to obtain basic data for developing an optimal acupuncture method for MCI treatment.

## Methods/design

### Aims

We intend to obtain basic data for developing an optimal acupuncture treatment for MCI by comparing the effects of different acupuncture treatment methods (variable acupoint specificity, needle duration, and electrical stimulation) on cognitive function in MCI patients. Our study will indicate whether it is feasible to randomize participants to different acupuncture treatments for MCI and suggest whether acupuncture is an acceptable treatment for the included participants. The results of this study will be the basis of a future clinical trial to investigate the effects of optimal acupuncture treatment for MCI.

### Hypothesis

The null hypothesis is that randomization of patients into four equal groups each receiving a different acupuncture protocol is not feasible and/or acupuncture is not safe for MCI patients and different acupuncture treatment methods will provide similar improvements in cognitive function in MCI patients.

### Study design and setting

This study is a prospective, outcome-assessor-blinded, parallel-arm, single-center (DongShin University Gwangju Korean Medicine Hospital, Republic of Korea), randomized controlled clinical trial with a 1:1:1:1 allocation ratio. A total of 32 participants, who meet the inclusion and exclusion criteria, will be randomly allocated to a basic acupuncture (BA), an acupoint specificity (AS), a needle duration (ND), or an electroacupuncture (EA) group (*n* = 8 each). The patients will receive acupuncture treatment once per day, 3 days/week for 8 weeks.

The outcome measure will be improvement in cognitive function evaluated using the Korean version of the Alzheimer’s Disease Assessment Scale—cognitive subscale (ADAS-K-cog) and the Korean version of the Montreal Cognitive Assessment (MoCA-K), and improvement in scores on the Center for Epidemiological Studies Depression (CES-D), Korean Activities of Daily Living (K-ADL), Korean Instrumental Activities of Daily Living (K-IADL), and European Quality of Life Five Dimension Five Level (EQ-5D-5L) scales. All scores will be recorded at baseline (before intervention), 8 weeks after the first intervention (i.e., at the end of the intervention period), and 12 weeks after completion of the intervention.

The design of this study, including outcomes measured and evaluation schedules, is based on the designs of several previous studies that have evaluated acupuncture treatment for cognitive impairment [11, 12, 15]. This manuscript has been written in accordance with the Standard Protocol Items: Recommendations for Interventional Trials (SPIRIT) and Consolidated Standards Of Reporting Trials (CONSORT) 2010 guidelines [16, 17] (see Additional file 1).

This study protocol complies with the principles of the Declaration of Helsinki and Korean Good Clinical Practice guidelines. The trial has been registered at http://cris.nih.go.kr (registration number: KCT 0003430; registration date: 16 January 2019). The study design is summarized in Figs. 1 and 2.

**Fig. 1 Fig1:**
[figure not shown]
Flow chart of the trial

**Fig. 2 Fig2:**
[figure not shown]
Standard Protocol Items: Recommendations for interventional Trials Statement (SPIRIT) figure showing the enrolment, interventions, and data collection

### Participant recruitment

Participants will be recruited at the DongShin University Gwangju Korean Medicine Hospital in the Republic of Korea. The study will be advertised through local newspapers, the Internet, and posters in communities and hospitals. Interested individuals will learn how to participate in this clinical trial through telephone calls or visits to our hospital. During visits to the clinical research center of DongShin University Gwangju Korean Medicine Hospital, the clinical research coordinator (CRC) will explain the study to the participants, who will be asked to voluntarily sign an informed consent form before participation. In order for the enrolled participant to be able to complete treatment and evaluation, the CRC will adjust the treatment and evaluation schedule of the enrolled participant to facilitate participation in this study. Every time the enrolled participant visits, the CRC will explain the next visit’s schedule; and the day before the visit, the CRC will remind the enrolled participant of the schedule by telephone. The CRC will continuously monitor the medical condition of enrolled participants to ensure adherence to the intervention protocols.

### Inclusion criteria

Participants meeting all of the following criteria will be included in this trial: male or female aged 55–85 years; fulfillment of the Petersen diagnostic criteria for MCI [1] (i.e., subjective memory complaint, normal general cognitive function, objective memory impairment, not severe enough to interfere with ADL, and no dementia) with memory impairment for at least the 3 months preceding enrollment; score of 20–23 on the Korean version of the Mini-Mental State Examination (MMSE); score of 0–22 on the MoCA-K; sufficient language fluency to reliably complete all study assessments; and willingness to sign the informed consent form.

### Exclusion criteria

The exclusion criteria are as follows: dementia diagnosed in accordance with the *Diagnostic and Statistical Manual of Mental Disorders* fourth edition; history of brain lesions that might cause cognitive impairment (e.g., traumatic brain injury, stroke, intracranial-space-occupying lesions, or congenital mental retardation); presence of cancer and/or serious cardiovascular, cerebrovascular, liver, or kidney disease; history of treatment for alcohol/drug dependency or mental diseases (e.g., schizophrenia, serious anxiety, or depression) in the 6 months preceding enrollment; current treatment for MCI (e.g., medication, acupuncture, or cognitive training); difficulties in assessment due to visual or hearing impairment; being unfit for acupuncture (e.g., blood-clotting abnormalities (e.g., hemophilia), scalp infection, or presence of a pacemaker); and concurrent participation in other clinical trials.

### Dropout criteria

Participants will be dropped from the trial under the following conditions: less than 75% compliance with the protocol procedures (i.e., participating in fewer than 18 of the 24 scheduled treatment sessions); occurrence of a serious adverse event (SAE); reluctance to continue the trial; incomplete data that could influence the trial; large error in protocol or significant deviation in implementation; or if the principal investigator (PI) or institutional review board (IRB) decide to terminate their participation in the trial.

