### Statistical analysis

A statistician, who is not involved in data collection, will analyze the final data. We will perform a full analysis (FA) set to assess efficacy and a supplementary per-protocol (PP) analysis. We will compare the results of statistical analyses between the PP group and the FA group, and confirm whether there is a statistically significant difference between groups. If there is a significant difference between the PP and FA groups, the cause will be reviewed and reflected in the efficacy assessment. All statistical analyses will be performed using SPSS version 21 software.

Baseline characteristics will be described and compared among the groups. Continuous data will be presented as the mean and standard deviation, and compared using the independent *t* test or Wilcoxon rank-sum test. Categorical data will be presented as the frequency and percentage, and compared using the chi-square or Fisher’s exact test.

Within each group, changes in ADAS-K-cog, MoCA-K, CES-D, K-ADL, K-IADL, and EQ-5D-5L scores at 8 weeks (i.e., the end of the intervention) and 20 weeks (i.e., 12 weeks after the end of the intervention) after the start of the intervention will be analyzed relative to baseline scores using paired *t* tests or Wilcoxon signed-rank tests. The degree of change at each time point will be evaluated by repeated-measures analysis of variance and two-sample *t* tests or Wilcoxon rank-sum tests. Subanalyses will be performed according to participant age. All reported *P* values will be two-tailed with 95% confidence intervals. *P* < 0.05 will be considered statistically significant.

Missing values will be obtained using the last observation carried forward method. Interim analyses will not be performed.

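### The dropout rule takes randomised participants out of the trial, not just out of treatment, without saying whether they are still assessed or stay in the full analysis set

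*Protocol article*

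**What the plan says.** Under Dropout criteria, the rule opens: "Participants will be dropped from the trial under the following conditions: less than 75% compliance with the protocol procedures". The threshold is spelled out as "participating in fewer than 18 of the 24 scheduled treatment sessions". Further triggers are "occurrence of a serious adverse event (SAE); reluctance to continue the trial; incomplete data that could influence the trial" and "large error in protocol or significant deviation in implementation", followed by a decision of the principal investigator or the review board.

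Under Statistical analysis, the plan is: "We will perform a full analysis (FA) set to assess efficacy and a supplementary per-protocol (PP) analysis". It continues: "We will compare the results of statistical analyses between the PP group and the FA group". If the two differ significantly, the cause is to be reviewed and taken into account in judging efficacy. On missing data: "Missing values will be obtained using the last observation carried forward method".

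The Randomization section places allocation after the baseline measurements. Study design and setting and Outcome measurements give three scoring times: baseline, week 8 (end of treatment) and 12 weeks after treatment ends (week 20).

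**The concern.** Leaving treatment and leaving the trial are different events, and the rule merges them. A participant who misses sessions or has a protocol deviation can still be scored at weeks 8 and 20. The rule takes that person out of the trial, and the article provides for no later assessment.

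Two triggers make poor sense as rules for stopping treatment. Incomplete data is purely a matter of data. Low attendance may become certain only at the last session, when no treatment is left to stop. Applied then, the rule can affect only follow-up or analysis.

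The comparison of the four arms as randomised is at stake. Each arm has 8 people, and those removed are chosen by what happened to them after allocation. An analysis plan written later can settle who belongs to the FA set, but it cannot recover assessments that were never made.

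**Working it through.** **Stated figures.** 3 sessions per week × 8 weeks = 24 sessions, and 18/24 = 75%, as stated. 4 arms × 8 = 32, as stated. No figure in the article is wrong on this point.

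**When the attendance trigger bites.** Six missed sessions leave 24 − 6 = 18 attended, which is allowed. Seven leave 17, which is not. The trigger is therefore certain at the seventh missed session. That can come as early as session 7 (week 3) or as late as session 24 (week 8), so removal before the week-8 assessment is quite possible.

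**Reading A: dropped participants leave the FA set.** The FA set then holds people with adequate attendance, sufficiently complete data and no major deviation, which is close to a PP set. The FA-PP comparison has little to compare, and LOCF has few missing values to fill. The incomplete-data trigger fits worst, because it removes people for the problem that LOCF is meant to handle.

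**Reading B: dropped participants stay in the FA set but are not assessed.** LOCF carries the last score forward. For someone dropped before week 8, that score is baseline:
- change at week 8 = baseline − baseline = 0
- change at week 20 = baseline − baseline = 0

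Someone dropped between weeks 8 and 20 is given the week-8 change again at week 20.

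**Weight of one participant.** 1/8 = 12.5% of an arm.

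**Illustration (all values assumed; the article gives none).** Let k of 8 be dropped before week 8. The others improve by a mean of a points, and the dropped participants would truly have improved by d.
- As randomised: [(8 − k)a + kd]/8
- Reading A reports a, an error of k(a − d)/8
- Reading B reports (8 − k)a/8, an error of −kd/8

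With k = 2 and a = 3, Reading A reports 3.0 and Reading B reports (6 × 3 + 2 × 0)/8 = 2.25:

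| d (assumed) | As randomised | Error, Reading A | Error, Reading B |
|---|---|---|---|
| 1.5 | (18 + 3)/8 = 2.625 | +0.375 | −0.375 |
| 0 | 18/8 = 2.25 | +0.75 | 0 |
| −3 | (18 − 6)/8 = 1.5 | +1.5 | +0.75 |

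The error under Reading B can take either sign, and it is zero only if dropped participants truly do not change. Under Reading A it is upward here because each assumed d is below a.

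**How often an arm might be touched (assumed removal rates).** The chance that a given arm of 8 loses at least one participant is 1 − (1 − p)^8. This is 57% at p = 10%, 83% at 20% and 94% at 30%.

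**The case against.** The strongest reply is that the article never says dropped participants leave the FA set. It plans separate FA and PP analyses and compares them, which makes sense only if the two sets differ. LOCF is itself a rule for people who leave, and everyone has a baseline score to carry forward. On that reading the sections are compatible. A journal article may also leave set definitions to a fuller document.

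Much of this stands. A reader might infer that the dropout rule turns the full analysis into a PP analysis, or that it flatly contradicts the imputation plan. Both inferences need exclusion from the FA set, which the article does not state.

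A reader might also infer a definite bias. Suppose attenders gain 3 points and non-attenders 0, and electroacupuncture loses 3 people while basic acupuncture loses 1. Analysing attenders alone gives 3 − 3 = 0. Under LOCF from baseline, the difference is (5 × 3)/8 − (7 × 3)/8 = 1.875 − 2.625 = −0.75, exactly the assumed truth. That masking therefore arises only under exclusion. The article gives no rates to show that removals differ by arm.

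Nor is it supported that safety and attendance information is lost. The adverse event section has all events during the trial documented, and the low attendance or serious event that triggers removal is already known. What may be lost is follow-up after departure.

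The reply does not settle whether dropped participants are still assessed. Under the favourable reading, the rule itself still replaces obtainable scores with carried-forward ones. That the study is a pilot lowers the stakes for efficacy claims, but its aim is still to compare the arms as a basis for a later trial.

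**Conclusion.** The concern holds in a limited form. The rule removes randomised participants from the trial for post-randomisation reasons, using criteria that mostly belong to a PP definition, and the article does not reconcile this with its FA analysis and LOCF. Exclusion from the FA set would leave FA and PP nearly the same. Retention without assessment would fix the change of anyone dropped before week 8 at zero for both time points. Either way, outcome data or a place in the analysis is lost avoidably.

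The only size that follows from the article is 12.5% of an arm per participant. The illustrated errors rest on assumed outcomes, and the direction and magnitude of any real bias cannot be derived. The conclusion assumes that removal from the trial ends assessment, which is the plain sense of the wording but is not stated outright. Whether and when treatment should stop is a clinical matter and is not judged here.

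**What to change.** Reconcile the Dropout criteria and Statistical analysis sections as follows:
- Distinguish stopping study treatment from leaving the trial. Clinical decisions on stopping treatment stay as they are.
- Invite every randomised participant to the scheduled week-8 and week-20 assessments and to adverse event follow-up, unless consent is withdrawn.
- Analyse all randomised participants in the FA set, in the arm to which they were allocated.
- Use the 18-of-24 threshold, incomplete data and deviations only to define the PP set.

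The cost is a wording change, which under Quality assurance needs review board approval, and a few assessment visits for people who have stopped treatment. Those time points are already in the schedule, but the article does not say whether funding, which it describes as limited, covers visits for dropped participants. The FA estimate may turn out smaller than one based on completers. The trial status section describes the trial as ongoing, so the change helps only participants whose assessments are still to come.

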### Ethical considerations

This study has been approved by the IRB of DongShin University Gwangju Korean Medicine Hospital, Republic of Korea (DSUOH-051). The purpose and potential risks of this clinical trial will be fully explained to the participants and their families. All participants will be asked to provide written informed consent before participation.

### Randomization

After acquiring written informed consent and completing the baseline measurements, the 32 enrolled participants will be assigned serial numbers generated by SPSS software version 21 (IBM Corp., Armonk, NY, USA) and randomly allocated to one of the four study groups (*n* = 8 each). The serial number codes will be inserted into opaque envelopes, which will be sealed and stored in a double-locked cabinet. These envelopes will then be opened in the presence of the patient and a guardian.

### Implementation

The CRC will generate the allocation sequence, enroll participants, and assign participants to interventions.

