### Occurrence of adverse events

Adverse events (AEs) are undesirable and unintentional signs, symptoms, or diseases that appear during or after treatment in a clinical trial. Participants in this study will be required to voluntarily report any AEs. All AEs that occur during the trial will be documented. AEs that could occur in this study include skin irritation, bleeding, local hematoma, pallor, sweating or dizziness, fainting during acupuncture treatment, needle retention after treatment, continuous severe pain for more than 1 h after acupuncture treatment, or objective worsening of existing symptoms. The CRC will record all AEs in detail, including the time and date of occurrence, degree of severity, any measures related to treatment of the AE, and any potentially causal relationship between the trial and AE, as well as report all AEs to the PI and relevant IRB. In the case of SAEs, defined as those causing severe disability or malfunction, appropriate measures will be taken and the incident will be immediately reported to the PI and relevant IRB. If an AE is determined to occur because of the clinical trial, participants will notify the CRC and the PI and be compensated.

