### Quality assurance

This protocol has been reviewed and revised several times by experts on acupuncture, neurology, statistics, and methodology. Before the trial, all researchers will be required to attend a series of training sessions, which will ensure that the personnel involved fully understand the trial protocol and standard operating procedures of the study. The Data Monitoring Committee (DMC) will comprise the PI, the CRC, and a researcher who are not involved in the data collection portion of the clinical trial. The DMC, which is independent from the sponsor and competing interests, will manage the data to ensure its validity. In the event that the protocol described herein is revised, the revisions will require approval from the IRB of DongShin University Gwangju Korean Medicine Hospital.

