### Confidentiality and data management

All identification records of the participants will be kept confidential. When the results of the study are published, the identification records will be accessed with IRB approval and the participants’ names will appear as initials to protect individuals’ identities, if necessary. All documents related to the trial, including case report forms (CRFs), will be recorded and labeled with participant identification codes and will not reveal the names of participants. The serial number codes will be stored in sealed, opaque envelopes and kept in a double-locked cabinet. All participant data will be recorded in Excel files by the CRC. All data will be checked by the CRC and rechecked by a researcher, both of whom are not included in this study’s data collection phase to ensure the reliability of the data. Continuous data will be coded as data values and categorical data will be coded as number sets for each item by a statistician who is not involved in the data collection phase of this clinical trial. The entry and coding of data will be double-checked. Electronic data will be stored on a password-protected computer. Anyone who is not approved by the IRB will not be able to access the data. In addition, raw data (i.e., CRFs) will be stored in a cabinet until the end of the study. Written informed consent for the publication of individuals’ details and accompanying images will be obtained from the participants.

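### The coordinator who enrols participants also generates the allocation sequence and assigns the arms, so allocation is not concealed from the person who controls enrolment

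*Protocol article*

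**What the plan says.** Three sections of the protocol article set out allocation.

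- **Implementation** gives all three allocation tasks to one role: "The CRC will generate the allocation sequence, enroll participants, and assign participants to interventions".
- **Participant recruitment** puts that role in front of candidates before consent: "the clinical research coordinator (CRC) will explain the study to the participants, who will be asked to voluntarily sign an informed consent form before participation". The CRC also adjusts enrolled participants' treatment and evaluation visits.
- **Randomization** describes the order of events ("After acquiring written informed consent and completing the baseline measurements, the 32 enrolled participants will be assigned serial numbers generated by SPSS software version 21") and the concealment device: "The serial number codes will be inserted into opaque envelopes, which will be sealed and stored in a double-locked cabinet". On opening it says: "These envelopes will then be opened in the presence of the patient and a guardian". It names nobody other than the CRC who prepares the envelopes or holds the keys.

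The **Blinding** section mentions selection bias. Its safeguard is to involve only people with no conflicting interests and no prior view. Only the outcome assessor is blinded.

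On data roles, **Occurrence of adverse events** says "The CRC will record all AEs in detail", and **Confidentiality and data management** says "All participant data will be recorded in Excel files by the CRC". Yet **Quality assurance** says "The Data Monitoring Committee (DMC) will comprise the PI, the CRC, and a researcher who are not involved in the data collection portion", and the data management section likewise places the CRC, as first checker, outside data collection.

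**The concern.** Allocation concealment means that whoever decides whether and when a candidate enters the trial cannot know the next arm. Sealed opaque envelopes achieve this only against someone who has not seen the sequence. Here the person who makes the list is the person who enrols.

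Someone who knows the next arm can bring a candidate forward, hold one back, or read a borderline eligibility item more or less strictly. Analysis cannot repair the resulting imbalance, because it may lie in features that were never measured. Two of the trial's purposes are exposed: showing that randomisation to these four treatments is feasible, and comparing cognitive change between arms as the basis for a later trial.

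**Working it through.** **1. Who does what**

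| Task | Role | Section |
|---|---|---|
| Generates the sequence | CRC | Implementation |
| Explains the study to candidates | CRC | Participant recruitment |
| Enrols | CRC | Implementation |
| Adjusts treatment and evaluation visits | CRC | Participant recruitment |
| Assigns to arms | CRC | Implementation |
| Prepares envelopes, holds keys | nobody separate named | Randomization |

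**2. Does any stated safeguard separate these tasks?**

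- *Sealed envelopes in a locked cabinet:* they conceal the arm from patients and guardians, not from the author of the list.
- *Opening before the patient and guardian:* this limits swapping an envelope at that moment. It does not affect who is in the room that day.
- *Consent and baseline first:* this keeps the arm from influencing the baseline score, but the order in which candidates reach that step remains in the CRC's hands.
- *Staff without prior views:* an assurance about people, not a procedure.
- *Blinded assessor:* acts on detection bias, not selection.

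None of them separates sequence generation from enrolment.

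**3. How predictable is the next arm?**

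The plan's own count is consistent: 4 arms × 8 = 32. The sample size rests on feasibility, so there is no power figure to reproduce.

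- By chance: 32 × 1/4 = 8 correct guesses (25%).
- Without the list, but seeing past allocations and knowing that each arm ends at 8: always guess the arm with most places left. Over 20,000 simulated random orders of 4 × 8, the mean was 12.1 correct; 12.1/32 = 38%. This assumes a simple random order of the 32.
- With the list: 32/32 = 100%.

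**4. How far could steering move a result?**

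Inputs: n = 8 per arm (Study design and setting). The documents give no outcome SD and no prognostic difference, so the difference d between a steered participant and the one displaced is an assumption, shown over a range.

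- Shift in one arm's mean for k steered participants = k × d / 8.
- Standard error of an 8 v 8 difference = SD × √(1/8 + 1/8) = SD × √(2/8) = 0.5 SD.

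| Assumed d | k = 1 | k = 2 | k = 2 as a share of the SE |
|---|---|---|---|
| 0.5 SD | 0.0625 SD | 0.125 SD | 25% |
| 1.0 SD | 0.125 SD | 0.25 SD | 50% |
| 1.5 SD | 0.1875 SD | 0.375 SD | 75% |

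These are shifts in one arm. If the displaced participant lands in the arm being compared, the difference moves twice as far (at d = 1 SD, 2 × 0.125 = 0.25 SD per participant).

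A second way to see it: suppose a share f of one arm's places is filled from the better half of a normal prognosis distribution, whose mean is √(2/π) = 0.80 SD. The arm mean shifts by 0.80 × f: 0.08 SD at f = 0.10, 0.20 SD at f = 0.25 and 0.40 SD at f = 0.50.

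**5. Data roles, side by side**

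The CRC records every adverse event and enters all participant data. The CRC is also described, in two sections, as outside data collection, and is the first checker of the entries. The statement about adverse events and the statements about data collection cannot both stand, and a check by the person who made the entries is not an independent check.

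**The case against.** **The Randomization section could describe a single batch.** Its wording about the 32 enrolled participants might mean that everyone is randomised together once recruitment closes, which would remove foreknowledge. This is unlikely: Trial status gives recruitment from February 2019 to December 2020, and each envelope is opened with its patient.

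**Incentive and discretion are limited.** This is a pilot that declares itself too small to establish efficacy, all four arms are real acupuncture, the cognitive entry criteria are fixed score bands, and assessors are blinded. All of this stands and lowers the likely consequence. It does not restore concealment. Timing can still be steered, and eligibility keeps judgement items such as language fluency, seriousness of other disease and fitness for acupuncture.

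**Stronger readings that the documents do not support:**

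- *The envelopes conceal nothing.* They still hide the arm from patients until opening.
- *The CRC takes consent.* The article says that the CRC explains the study; it does not say who takes consent.
- *The CRC certainly knows all 32 assignments.* The text states the opportunity. It does not say whether the list can be consulted after it is made.
- *A few steered participants would decide the ranking of the arms.* The plan has no ranking rule and gives no expected gap between arms. Two participants at d = 1 SD move one arm's mean by half a standard error.
- *There is no second data check.* A recheck by a researcher is planned.
- *The monitoring committee is claimed to be independent of the trial team.* The claim covers only the sponsor and competing interests. The committee's membership can be criticised, but that is not an allocation issue.

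**Conclusion.** The concern holds for the person who controls enrolment. The article states outright that one role generates the sequence, enrols and assigns, so this is a stated design flaw and not detail lost in condensing a longer protocol. The route to bias is the timing or deferral of enrolment. Nothing in the documents shows that it was used.

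For scale, the next arm is 100% predictable with the list, against about 38% for an enroller without it and 25% by chance. Each steered participant shifts an arm mean by 0.125 SD if the assumed difference is 1 SD (0.0625 to 0.1875 SD for 0.5 to 1.5 SD), against a standard error of 0.5 SD. These shifts are illustrations, not estimates of actual bias. Because analysis cannot recover lost concealment and the remedy is cheap, it should be corrected before further places are allocated.

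The contradiction about the CRC's part in data collection is real but separate and lesser, and adds nothing to the weight of the allocation point.

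**What to change.** 1. Have an existing person with no part in recruitment or enrolment generate and hold the sequence and prepare sequentially numbered, sealed, opaque envelopes. The researcher described as outside data collection is one candidate, once it is confirmed that this person does not recruit. The independent statistician is another, but the Blinding section describes the statistician as uninvolved in the trial's execution, so that wording would need adjusting.
2. Limit the CRC to enrolling, and to opening the next numbered envelope once consent and baseline are recorded. The order of consent, baseline and allocation is already in the plan; the change is that the CRC no longer knows what is inside.
3. For places not yet allocated, have that person re-randomise the remaining slots, keeping 8 per arm (8 minus those already allocated in each arm). With a fixed total per arm, the last places stay partly predictable from the running counts; say so.
4. Report allocations already made under the present procedure as a limitation, with their number.
5. Separately, reconcile the statements that place the CRC outside data collection with those that have the CRC record adverse events and enter all data. Do not count the CRC's check of the CRC's own entries as one of two independent checks; the researcher's recheck remains as the independent one.

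Cost: some hours of an existing person's time, new envelopes for the remaining places, and an amendment through the IRB route that Quality assurance already provides. No added participants or visits.
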